### Recruitment

Stroke survivors and their primary family caregivers will be recruited together as participant dyads from participating wards. A recruitment poster will be displayed at the nursing station of each ward and a secure participant response drop-box placed underneath. Participant dyads who are interested in this project will be asked to fill in a response slip that includes their contact details and place it in the drop-box. Upon receiving the response slip, a research recruiter (the secretary in each ward), who is blinded to group allocation and has no interest in the outcome of the study, will contact participant dyads to confirm their participation. On confirmation of participation, an intervention nurse will check the eligibility of participant dyads, explain the project to them and seek informed consent. An intervention nurse will also allocate each participant dyad to either the intervention group or the usual care group after baseline data collection using the sequentially numbered, opaque, sealed envelopes.

### Data collection methods

Baseline data collection will be conducted at the hospitals through self-administered questionnaires. The researcher ([name]) will prepare a drop box for each ward. Participants will be instructed to place their completed questionnaire in a sealed envelope to maintain confidentiality and to put the envelope into the drop box. The researcher will collect completed baseline questionnaires on a weekly basis. For 12-week and 24-week follow-up data collection, the researcher ([name]) will mail a questionnaire to participants with pre-paid and pre-addressed envelopes. Participants will be instructed to return the completed questionnaire to the researcher by post.

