### Randomization

We will allocate eligible participant dyads to the intervention group or the control group using simple randomization, with an equal allocation ratio of 1:1, using IBM SPSS Statistics version 25 random sampling and allocation methods. A research associate who is not involved in recruitment, intervention allocation or outcome assessment will generate the random numbers. Allocation concealment will be ensured by the research associate putting the group allocation into sequentially numbered, opaque, sealed envelopes to inform the intervention nurse after baseline data collection for each dyad.

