### Usual care

Participants in the usual care group will receive the usual transitional discharge plan that includes verbal stroke-related education and a follow-up telephone call at the end of the first and the fourth week after discharge to home. For usual care, other registered nurses, who are not intervention nurses, will conduct the discharge plan and follow-up.

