#### Secondary outcomes

2.1Quality of life: This outcome will be measured using the short version of the Stroke-Specific Quality of Life Scale (SSQoL-12). The SSQoL-12 is a self-assessment scale comprising physical domain (6 items) and psychosocial domain (6 items) [29]. The SSQoL-12 has good criterion validity and internal consistency (Cronbach’s α 0.77–0.89).2.2Functional ability: This outcome will be measured using (1) the Chinese version of the Barthel Index (BI) for ADL, (2) the Multilevel Lawton Instrumental Activities of Daily Living (Lawton IADL), and (3) the Social Support Rating Scale (SSRS). The BI comprises 10 items and is a valid tool to evaluate the ADL of stroke survivors [30, 31]. It has been translated into Chinese with acceptable internal consistency (Cronbach’s α of 0.916) [32]. The Lawton IADL is an appropriate instrument with eight categories to assess independent living skills [33]. It has been used and proven in the Chinese population with a satisfactory Cronbach’s alpha of 0.739 [34]. The SSRS was developed in China and is widely used with high validity (Cronbach’s alpha 0.83 to 0.90) and reliability (test–retest reliability 0.92) [35, 36].2.3Stroke-related health knowledge: This outcome will be measured using the Chinese Stroke Prevention Knowledge Questionnaire (SPKQ). The SPKQ comprises 25 items using close-ended questions to assess patients’ stroke-related knowledge. It has been used in the Chinese population with a validity index of 0.89 and Cronbach’s α of 0.86 [37].2.4The number of deaths, adverse events and unplanned hospital admissions: The adverse events will be limited to secondary strokes, falls, ulcers and urinary tract infections to reflect the nurse-led intervention to prevent post-stroke associated complications. These outcomes will be recorded by participants on the “Adverse Events Form” and verified by an intervention nurse.

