### Intervention fidelity

Standardized training and written guidelines for intervention nurses will enhance adherence to the study protocol. A “Stroke Health Coaching Diary” and a written education booklet to reinforce health coaching activities for stroke survivor-caregiver dyads in the intervention group will be used to help them adhere to the intervention protocol.

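### The stroke-knowledge questionnaire is answered unsupervised at home at follow-up, while a trial-supplied education booklet is described only for the coached arm, so the SPKQ difference can mix retained knowledge with access to that booklet

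*Protocol article*

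**What the plan says.** All references are to the protocol article.

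- **Outcome.** Secondary outcomes, item 2.3, measures stroke-related health knowledge with the SPKQ: "The SPKQ comprises 25 items using close-ended questions". Outcomes measures sets the assessments at baseline, 12 weeks and 24 weeks.
- **Baseline mode.** Data collection methods: "Baseline data collection will be conducted at the hospitals through self-administered questionnaires". Forms are sealed and left in a ward drop box.
- **Follow-up mode.** Same section: the researcher "will mail a questionnaire to participants with pre-paid and pre-addressed envelopes", and "Participants will be instructed to return the completed questionnaire to the researcher by post". No other follow-up route is described.
- **Order of events.** Under Randomization, sealed envelopes serve "to inform the intervention nurse after baseline data collection for each dyad". Arm-specific material therefore cannot reach a dyad before its baseline form.
- **Coached arm.** Intervention fidelity lists a coaching diary and "a written education booklet to reinforce health coaching activities for stroke survivor-caregiver dyads in the intervention group".
- **Usual care.** Usual care is "the usual transitional discharge plan that includes verbal stroke-related education", with two follow-up calls. Written material is not mentioned.
- **Blinding.** Evaluator blinding leaves dyads unblinded and blinds the researcher who collects and analyses the outcomes.
- **Analysis.** Data analysis specifies intention to treat and a mixed model for repeated measures, and reports the time-by-group interaction.

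**The concern.** The SPKQ is described as a measure of what patients know. Unlike a rating of confidence, burden or function, a knowledge item can be answered by consulting a text or by having someone else supply the answer. At follow-up the form is completed at home with nobody from the trial present, and on the article's description one arm has been given a written text about its stroke education and the other has not.

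If some coached survivors consult that text, their scores rise for a reason other than what they have retained. The trial could then report a knowledge gain that is partly a matter of which arm held the booklet. The expected direction is one-sided, in favour of coaching. The blinded researcher offers no protection, because that person posts and receives forms and does not see them completed.

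**Working it through.** **Step 1. Where the arms differ, and when.**

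| | Baseline | 12 and 24 weeks |
|---|---|---|
| Where completed | In hospital, self-administered | At home, returned by post |
| Supervision described | None | None |
| Booklet, coached arm | Not yet (allocation follows baseline) | Yes |
| Booklet, usual care | No | None described |

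Lack of supervision is common to all time points. What changes between baseline and follow-up, in one arm only, is possession of the booklet.

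**Step 2. Whether the planned model removes it.** Let B be the mean rise in the coached arm's follow-up score due to looking answers up. Then:

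- expected group difference at baseline = 0, by randomisation;
- expected group difference at follow-up = (true difference in retained knowledge) + B;
- time-by-group effect = follow-up difference − baseline difference = (true difference) + B.

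Adjusting for baseline value, age, gender, education, insurance and comorbidities leaves B in place, because it arises after allocation and in one arm.

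**Step 3. How large B could be.** The article gives no SPKQ standard deviation, expected score, booklet text or look-up rate, so there is no plan figure to reproduce and B cannot be calculated. For illustration only, assume one point per item. Let f be the share of coached survivors who consult the booklet and g the items each of them gains, so B = f × g. A rise in correct answers from 70% to 90% gives g = 25 × 0.20 = 5. From 60% to 90%, g = 25 × 0.30 = 7.5. A modest gain is taken as g = 2.

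| f | g = 2 | g = 5 | g = 7.5 |
|---|---|---|---|
| 0.10 | 0.2 | 0.5 | 0.75 |
| 0.25 | 0.5 | 1.25 | 1.88 |
| 0.50 | 1.0 | 2.5 | 3.75 |

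If f = 0, or the booklet answers no SPKQ item, B = 0.

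**Step 4. What that could do to a test.** The sample size section plans 70 per arm with 10% dropout, so 70 × 0.90 = 63 analysed per arm. Assume no true difference in retained knowledge, an SD of 4 and a simple two-sided comparison at one visit (cruder than the planned model, and ignoring the extra spread that look-up creates). For f = 0.10 and g = 5:

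- standard error = 4 × √(2/63) = 0.713;
- B / standard error = 0.5 / 0.713 = 0.70;
- chance of p < 0.05 = Φ(0.70 − 1.96) + Φ(−0.70 − 1.96) = 0.104 + 0.004 ≈ 0.11, against a nominal 0.05.

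Over SDs of 3 to 5 and g of 5 to 7.5, the corresponding chance is about 9–29% at f = 0.10, 29–94% at f = 0.25 and 80–100% at f = 0.50. These ranges show sensitivity to the assumptions. They do not estimate what this trial will see.

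**The case against.** **The article need not reproduce the instructions printed on its forms.** Correct, and the full protocol or the forms may already ask for answers from memory. The point does not rest on that silence. It rests on two stated choices, unsupervised completion by post and a booklet described for one arm, whose combination calls for a safeguard. If one is already printed, what remains is to record and report look-up.

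**The booklet's contents are not shown.** This stands. Table 1 lists the topics of the coaching sessions (second stroke, complications and medication among them), not the booklet's contents. Intervention fidelity says only that the booklet reinforces the coaching. Overlap with SPKQ items is plausible but inferred. The diary is described for recording and self-monitoring, not as a reference text.

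**Usual-care survivors can look things up too.** Also true. A reader might infer that usual care gets verbal education and nothing else, but the article says that the discharge plan includes verbal education, and other sources are open to both arms. This would dilute the imbalance. It would not necessarily remove it, since the booklet is described for one arm only.

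**Having a booklet to consult is part of the benefit.** Perhaps, but the outcome is defined as patients' knowledge. As collected, the score cannot separate knowledge held from a text at hand.

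**Only one secondary outcome is touched.** Agreed. The SSEQ measures self-efficacy and has no answers to look up.

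**Conclusion.** The point holds as a modest, inexpensive improvement to one secondary outcome. To the extent that coached survivors consult the booklet, the SPKQ difference can mix retained knowledge with access to trial material, in favour of coaching, and the planned model cannot separate the two. This assumes that the SPKQ travels in the mailed questionnaire (the only follow-up route described), that the booklet bears on at least some SPKQ items, and that usual care receives no comparable text.

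Three stronger readings are not supported:

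- A reader might infer that the SPKQ is in fact an open-book test for the coached arm and overstates the gain. The documents show the opportunity, not that anyone uses it.
- A reader might set the illustrated shift against the effect size of 0.5 in the sample size section. That figure belongs to the SSEQ; no SPKQ effect is planned.
- A reader might infer that a positive SPKQ result could mean that nothing was learned. Two coaching sessions before discharge, weekly calls and bi-weekly meetings make some real learning likely.

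The size of the bias therefore remains unknown, and the figures under working are illustrations on assumed inputs.

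**What to change.** On every SPKQ form still to be completed, identically in both arms:

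1. Print an instruction to answer the knowledge items from memory, without booklet, diary, internet or another person supplying answers. State that help with reading or writing is allowed, so that survivors with limb weakness are not deterred from returning the form.
2. Add one yes/no item asking whether any answers were looked up or supplied by someone else.

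In the analysis, keep the intention-to-treat comparison of all forms as the main SPKQ result and report the look-up item by arm. An analysis without the forms marked yes may be added, labelled as a non-randomised sensitivity analysis, because it selects on behaviour after randomisation that may differ by arm. Word the SPKQ conclusion to match what was found.

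**Cost.** One instruction, one item, one table row and one sensitivity analysis, with slightly more form burden. The item relies on honest answers, so some bias may remain.

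**Timing.** Forms already returned cannot be corrected. Trial status expected recruitment to end on 10 October 2019. Counting from that date, the last 12-week forms fall due about 2 January 2020 (84 days later) and the last 24-week forms about 26 March 2020 (168 days later), against a protocol version dated 20 January 2020. Unless recruitment was extended, the new wording could reach only some 24-week forms. For the rest, the remedy is a caveat in the report.

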### Data analysis

The intention-to-treat (ITT) approach will be adopted for data analysis. Statistical analysis will be performed using IBM SPSS Statistics version 25 and STATA software version 15. The normality of data will be assessed using normality plots. Percentages will be presented to summarise category data. Means and standard deviation, or medians and IQR, will be presented to describe countinous data with normal distribution and non-normal distribution respectively. Two group comparisons of demographic and clinical characteristics at baseline will be performed using Chi-square tests for category data and independent t-tests or non-parametric Mann-Whitney U-tests for data with normal distribution or non-normal distribution respectively.

The researcher will determine changes in outcome measures at baseline, and 12-week and 24-week follow-ups. To estimate mean changes over time in primary and secondary outcomes, linear mixed effect models for repeated measures will be used to assess differences between the two groups. Fixed effects in the model will include time, group, covariate(s) and the two-way interaction of group and time. The model will also include participant-level random effects to account for correlation between participants’ repeated measures over time. Value and confounders that include age, gender, educational level, insurance type, and number of comorbidities at baseline will be adjusted in this model. A *p* < 0.05 will be regarded as statistically significant for all statistical tests. Estimated mean differences, including 95% confidence intervals and *p*-values, will be reported for (time × group) interaction effects.

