**Methods:**

This is a single-blind, two-arm parallel randomized controlled trial of a nurse-led health coaching program versus routine care situated in two tertiary hospitals in Chongqing, China. Stroke survivors and their primary family caregivers will be recruited together as “participant dyads”, and the estimated sample size is 140 (70 in each group). The intervention includes a 12-week nurse-led health coaching program in hospital to home transition care commencing at discharge from the hospital. The primary outcome is changes in self-efficacy of stroke survivors at 12 weeks from the baseline. The secondary outcomes are changes in stroke survivors’ and quality of life, functional ability, stroke-related knowledge, the number of adverse events, and unplanned hospital admissions, and caregivers’ self-efficacy and caregiver-related burden at 12 weeks from the baseline. The outcomes will be measured at 12 weeks and 24 weeks from the baseline.

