### Sample size

The sample size is estimated on the basis of the primary outcome, stroke survivors’ self-efficacy, measured by the SSEQ [27]. We generated the estimated effect size of 0.5 based on a 7.5 point between-group change in SSEQ from baseline reported in a similar RCT by Lo et al. [42]. We also estimated a pooled SD of 6.42 based on the 95% confidence interval of the SSEQ score reported in the study. A type I error of alpha 0.05 and a power of 80% were used in the sample size calculation. We expect a 10% dropout rate. Therefore, we will require 70 dyads per treatment group. In total, we will recruit at least 140 participant dyads into the study.

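### As written, the reported time × group interaction is either essentially unadjusted or not the 12-week effect, so the promised baseline adjustment does not reach the primary estimate

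*Protocol article*

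**What the plan says.** The protocol article (Abstract, Methods) defines the target: "The primary outcome is changes in self-efficacy of stroke survivors at 12 weeks from the baseline". The Data analysis section then fixes four things:

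- Visits: "The researcher will determine changes in outcome measures at baseline, and 12-week and 24-week follow-ups".
- Mean model: "Fixed effects in the model will include time, group, covariate(s) and the two-way interaction of group and time". The only interaction named is group with time. There is no covariate × time term and no constraint that the groups share a baseline mean.
- Adjustment: "Value and confounders that include age, gender, educational level, insurance type, and number of comorbidities at baseline will be adjusted in this model". The first word of that sentence is not defined; the baseline score of the outcome is the likely meaning. Everything in the set is constant over time within a participant.
- Output: estimated mean differences with intervals and p-values "will be reported for (time × group) interaction effects".

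Within-person correlation is handled as follows: "The model will also include participant-level random effects to account for correlation between participants’ repeated measures over time". The section does not say outright whether the baseline measurement is a response, a covariate or both.

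**The concern.** A model, an adjustment set and a reported quantity are all stated, but they do not fit together. A covariate that is constant over time and enters only as a main effect shifts all of a participant's visits equally, so it drops out of any contrast between visits. The interaction is such a contrast. A team following the text could publish a 12-week result described as adjusted for baseline score, age, gender, education, insurance and comorbidity when it is close to the raw difference in mean change. It would also give up the precision that the baseline score, already collected, could supply. If baseline is instead kept out of the responses, the adjustment works, but the interaction answers a different question from the primary one.

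**Working it through.** **The plan's own figure.** Two-sided alpha 0.05 (sidedness is assumed; the article does not state it), power 80%, standardised effect 0.5: n = 2(1.960 + 0.842)² / 0.5² = 62.8, so 63 per arm. Allowing for 10% dropout, 63 / 0.9 = 70. This reproduces the stated 70 dyads per group. The checks below use 63 per arm.

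**Reading 1: baseline, week 12 and week 24 are all responses.** For participant i at visit j (0, 1, 2), with group G and time-constant covariates X:

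Y_ij = μ_j + γG_i + δ_jG_i + β′X_i + b_i + e_ij, with δ_0 = 0.

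Subtracting baseline from week 12:

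Y_i1 − Y_i0 = (μ_1 − μ_0) + δ_1G_i + (e_i1 − e_i0).

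β′X_i has gone, also when X includes the baseline score. With complete data this does not depend on the covariance structure. For any given β, the fitted intercept vector of a group is its vector of visit means minus the same constant β′X̄ at every visit, so a difference between visits is the raw difference.

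This was checked on three simulated trials: 63 per arm, participant variance 0.6, residual variance 0.4, an age and a sex effect, and a treatment effect of 0.5 at both follow-ups. Models were random-intercept REML. Entries are the week-12 interaction (standard error).

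| Trial | No covariates | Age, sex and baseline score as main effects | SE of baseline-adjusted week-12 regression |
|---|---|---|---|
| 1, complete | 0.33208 (0.160) | 0.33208 (0.160) | 0.135 |
| 2, complete | 0.36708 (0.161) | 0.36708 (0.161) | 0.145 |
| 3, complete | 0.33935 (0.156) | 0.33935 (0.156) | 0.131 |
| 1, 17 of 126 lost | 0.361 (0.171) | 0.378 (0.165) | 0.143 |
| 2, 13 of 126 lost | 0.344 (0.169) | 0.326 (0.163) | 0.149 |
| 3, 11 of 126 lost | 0.329 (0.164) | 0.312 (0.159) | 0.140 |

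With complete data the estimates also equal the raw difference in mean change. With dropout that depends on baseline score and age, the covariates move the estimate by about 0.02 and cut the standard error by 2.6% to 3.6%. True baseline adjustment does considerably more.

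**Reading 2: only weeks 12 and 24 are responses, with baseline score as a covariate.** The 12-week effect is then the group coefficient (week 12 as reference), and it is properly adjusted. The interaction coefficient is the week-24 effect minus the week-12 effect. In the three complete trials it was 0.199, 0.179 and −0.132, although the 12-week effect was set at 0.5 and the true interaction at zero.

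**Size of the precision loss under Reading 1.** Take equal outcome variance (set to 1) at baseline and week 12, and correlation r. Variance per participant is 2(1 − r) for change and 1 − r² for the baseline-adjusted score. The ratio is (1 − r²) / [2(1 − r)] = (1 + r)/2, and the standard error excess is 1/√[(1 + r)/2] − 1. The article gives no value of r. It reports an SSEQ test-retest coefficient of 0.806 (Primary outcomes), which is only a rough upper guide.

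| r (assumed) | Change | Adjusted | Ratio | SE excess of change contrast |
|---|---|---|---|---|
| 0.3 | 1.40 | 0.91 | 0.65 | 24% |
| 0.5 | 1.00 | 0.75 | 0.75 | 15% |
| 0.7 | 0.60 | 0.51 | 0.85 | 8% |
| 0.8 | 0.40 | 0.36 | 0.90 | 5% |

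**What this means for power depends on the scale of 0.5.** If it is in units of the SD of the score, power with 63 per arm (normal approximation) is 66% for change against 84% adjusted at r = 0.3, 80% against 90% at 0.5, and 95% against 98% at 0.7. If it is in units of the SD of change, the planned 80% holds at every r. The Sample size section does not settle this: "We also estimated a pooled SD of 6.42 based on the 95% confidence interval of the SSEQ score reported in the study", yet 7.5 / 6.42 = 1.17, not 0.5. That mismatch is a separate matter.

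**The case against.** The strongest defence is that the text never says baseline is a response. Adjusting for a baseline score fits most coherently with follow-up scores as the only responses, and the promised estimated mean differences could be model-based group differences at each visit. On that combination the plan would already be close to the fix below. This stands as a reason not to be categorical. It does not clear the text: the purpose given for the model is change over time across three visits that include baseline, and what is named for reporting is the interaction. Either literal route misses an adjusted 12-week difference.

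A reader might also infer more than the article supports:

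- That adjustment does nothing at all. This is exact only with complete data; the plan expects 10% dropout, where covariates have a small effect and may help if missingness depends on them.
- That the primary estimate is biased. Under randomisation the difference in mean change is unbiased.
- That simple randomisation makes imbalance in the baseline score likely. With 140 dyads it raises the variance of the baseline mean difference by only about 1/140, or 0.7%, over exactly equal arms.
- That the trial has only 66% power. This needs 0.5 to be in score-SD units and r to be 0.3. The article ties the effect to change: "We generated the estimated effect size of 0.5 based on a 7.5 point between-group change in SSEQ from baseline".
- That equal correlations between visits are imposed. This would follow from a random intercept alone, but the article writes of random effects in the plural and leaves their structure open, as an article may.

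**Conclusion.** The point holds in limited form. Followed as written, the plan yields a primary estimate that is either essentially unadjusted (baseline as a response) or aimed at the wrong contrast (weeks 12 and 24 only). The first reading is the more natural, but it is not stated. The harm is lost efficiency and a misleading label, not bias. On the first reading the standard error is about 5% to 24% larger than it need be for r from 0.8 to 0.3. That range rests on an assumed correlation and equal variances at the two visits. No shortfall from the stated 80% power is shown: if 0.5 is on the change scale, that power is kept and only extra efficiency is forgone. The change is worth making because it costs almost nothing.

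**What to change.** State that the undefined covariate is the baseline score of the outcome being analysed, and name the baseline-adjusted group difference at week 12 as the primary estimate. Either of two models gives it:

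1. Responses are the 12- and 24-week scores. Fixed effects are categorical time, group, group × time, baseline score, baseline score × time and the listed covariates. The primary estimate is the group difference at week 12.
2. Responses are all three visits, with group means constrained equal at baseline and the other covariates interacted with time. The primary estimate is the group difference at week 12.

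Report the interaction, if wanted, as a secondary description of whether the effect changes over time. The cost is wording and analysis only. Dyads with baseline data alone leave the likelihood in the first model but stay in the second, which may favour the second given the intention-to-treat aim.
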